To clarify the effect of tDCS on these different types of neuromuscular performance, we propose to evaluate the acute and repeated effects of tDCS during two tasks: an explosive task (jumps) and an endurance task (20-min cycling trial). The main objective is to compare the effects of tDCS applied over the left dlPFC with sham tDCS on the performance of the neuromuscular system. In the present protocol, the choice has been made to recruit participants with different backgrounds regarding sports practice, from sedentary people to high-level athletes in the targeted performance (parkour athletes for explosive performance or cyclists for endurance). Indeed, the tDCS effects on physical performance could also be a function of the initial level [23].

This study is a monocentre, sham-controlled, randomised, crossover, double-blinded superiority trial comparing active tDCS versus sham tDCS. It is divided into two parts: part A with the jumpers and part B with the cyclists. We hypothesise that the active tDCS sessions will improve motor performance and reduce neuromuscular fatigue. We will seek a better understanding of the factors that could cause tDCS effects to vary: stimulated brain area, exercise type (explosive vs enduring), tDCS configuration (cephalic vs extracephalic montage), and the number of tDCS sessions (single vs repeated stimulations).

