### Study procedure

#### Recruitment and randomisation

Firstly, subjects will be recruited by the sport research team. Information about the study, the neurostimulation technique, and the objectives of the research will be given to each subject by a trained psychiatry investigator. Enrolment date and timetable of visits will be scheduled directly with the volunteers.

After the informed consent is signed, a clinical exam will be conducted in order to verify the inclusion and exclusion criteria.

Subjects meeting the inclusion criteria will be randomised 1:1 into two (part A) or three (part B) groups using a minimisation technique with stratification according to their athletic level (hours of practice). Recruitment will be achieved when the number of subjects by groups is obtained.

After randomisation, a sequence of predefined codes will be generated by a computer. These predefined codes correspond to either the active or sham stimulation and will be used by the psychiatry staff to start the stimulator, allowing a double-blind study design. Each subject will present a control subject with the same randomisation sequence.

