### Sample size

Our sample size calculation is based on the primary efficacy outcome that relates to changes in motor performance before and after a tDCS session during an explosive task (jumps). In a previous study, Lattari et al. [22] showed an 11.2% improvement in the height of the CMJ following a tDCS session, corresponding to a difference of 3.9 cm (Table 1 of Lattari’s et al.). We expect a 15% improvement in our study corresponding to a difference of 5.1 cm. No difference is expected in the sham tDCS group. Considering a significance level of 5%, a power of 90%, and a standard deviation for paired differences of 6.5 (calculated from standard deviations, page 21, Table 1 with an hypothesis of a covariance of measures of 50%), 20 jumpers are included to meet the objectives of the study. Sample size calculation was performed on PASS 13 Power Analysis and Sample Size Software (2014) [39, 40] .

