### Data management and statistical analyses

All collected information will be registered in physical files (case report files (CRFs)), previously anonymised with the participant’s randomisation code in order to respect confidentiality at all times. Computer test data (BART, EEfRT) and physical test results will be collected in electronic format.

All researchers and trained staff called upon to collaborate in the tests are bound to secrecy.

Analyses will be performed using the SAS® 9.4 Software for Windows (SAS Institute©, Cary, NC, USA). Categorical variables will be described in terms of effective, absolute, and relative frequencies for each modality. Continuous variables will be described in terms of minimum and maximum, quartiles, means, and standard variations. Two-way repeated measures ANOVAs will be performed with the within-group factors of condition (a-tDCS/ c-tDCS/sham-tDCS) and moment (pre- and post-tDCS) for endurance performance or explosive performance. Bonferroni corrections will be employed to correct for type I errors due to multiple testing. The sphericity assumption will be tested using the Mauchly’s test and the Greenhouse-Geisser correction will be used whenever data sphericity is violated. The level of significance will be set at *p* ≤ 0.05. Subgroup analysis (level of practice) will be descriptive because of the small sample size of the study. Means and proportions will be calculated with their 95% confidence interval. All valid data will be used at different times of the study. There is no strategy for replacing missing data.

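### Athletic level stratifies allocation and fixes the recruitment mix but is left out of the main ANOVA, so any level difference in the tDCS effect enters the error term and costs some power

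*Protocol article*

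**What the plan says.** Under Recruitment and randomisation, the protocol article allocates participants "using a minimisation technique with stratification according to their athletic level (hours of practice"), into two groups in part A and three in part B. It adds: "Recruitment will be achieved when the number of subjects by groups is obtained". Under Study setting and overview, those groups are the levels of practice: amateur and high-level in part A; sedentary, amateur and high-level in part B. The mix of levels is therefore set by design, although the number per level is not given.

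The Background gives the reason for recruiting across levels: "the tDCS effects on physical performance could also be a function of the initial level". The Outcomes section lists the effect by motor expertise as a secondary criterion.

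Data management and statistical analyses names the main model as a two-way repeated-measures ANOVA "with the within-group factors of condition (a-tDCS/ c-tDCS/sham-tDCS) and moment (pre- and post-tDCS"). Level of practice appears there only as a descriptive subgroup analysis, and the reason given is the small sample.

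**The concern.** A factor that governs allocation and recruitment would normally appear in the model that tests the treatment effect. In a crossover the usual reason for this is weaker, because each person is their own control and any constant difference between levels drops out. What does not drop out is a difference between levels in the response to tDCS, which is the possibility that the Background raises.

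With only condition and moment in the model, such a difference counts as person-to-person inconsistency in the tDCS effect and goes into the error of the condition x moment test. Because the level mix is fixed by quota, this spread is not sampling variation of the average effect, so the standard error of that average is too large. At stake is power in a comparison of 20 people with little reserve. The ANOVA's factors are stated explicitly, so this is a choice in the text and not a detail left open.

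**Working it through.** **Inputs from the Sample size section.** "Considering a significance level of 5%, a power of 90"%; "We expect a 15% improvement in our study corresponding to a difference of 5.1 cm"; "No difference is expected in the sham tDCS group"; "a standard deviation for paired differences of 6.5" cm; 20 jumpers.

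**Assumptions not in the documents.** Ten jumpers per level. 6.5 cm taken as the SD within a level. A difference D between the two levels' tDCS effects, shown over a range. One active-versus-sham contrast tested two-sided at 5%, without the planned Bonferroni correction.

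**1. The plan's own figure.** For a paired t-test, the noncentrality is 5.1 / (6.5/√20) = 3.51 on 19 df. Power is 0.914, and 20 is the smallest n that reaches 0.90. The stated sample size reproduces.

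**2. Which level effects reach the error term.** A 3 x 2 repeated-measures F for condition x moment was computed on simulated data for 20 people.
- Adding a level main effect, or a level x moment effect common to all conditions, left F at 0.594.
- Adding a 5 cm level difference in one condition's post-stimulation value raised the error mean square from 48.5 to 56.0 and lowered F to 0.515.

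Only a level difference in the tDCS effect matters.

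**3. Size of the inflation.** With equal groups, one level responds by 5.1 + D/2 and the other by 5.1 − D/2. The expected variance without a level term is

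6.5² + (D²/4) × 20/19.

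At D = 5.1 this is 42.25 + 6.50 × 20/19 = 49.1, so the SD is 7.01, a variance 16% larger and a standard error about 8% larger.

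| D (cm) | effects in the two levels (cm) | SD without level | power without level | power with level |
|---|---|---|---|---|
| 0 | 5.1 / 5.1 | 6.50 | 0.914 | 0.912 |
| 2.55 | 6.375 / 3.825 | 6.63 | 0.907 | 0.912 |
| 5.1 | 7.65 / 2.55 | 7.01 | 0.886 | 0.912 |
| 10.2 | 10.2 / 0 | 8.34 | 0.786 | 0.912 |

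The column with level uses the within-level residual SD on 18 df. At D = 1 cm or below, the lost degree of freedom offsets the gain.

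**4. The other reading of 6.5 cm.** If 6.5 cm is the total SD and already contains the level difference, power without the term stays at 0.914. The term raises it to 0.923 at D = 2.55 and 0.952 at D = 5.1.

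**5. Rejection rate when the average effect is zero.** Without the level term and with 6.5 cm within level, it is about 3.6% at D = 5.1 and 1.4% at D = 10.2. An average of zero with D = 5.1 means +2.55 cm in one level and −2.55 cm in the other. If tDCS does nothing in either level, D is 0 and the rate is the nominal 5%.

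**Part B.** No SD is given, so no figure can be computed. The mechanism is the same with three levels.

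**The case against.** The strongest reply is that this was a reasoned choice. The trial is called exploratory, its main objective is active dlPFC stimulation against sham, expertise is secondary, and the sample is stated to be too small for more than descriptive subgroups. A pooled within-person ANOVA is a valid test of that objective. The point about validity stands. The small-sample reason does not settle the matter: it supports not testing effects within levels, but it does not require leaving the stratification factor out of the error term.

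The size is also open to challenge, and much of that challenge stands. The Background says only that the effect could depend on level and predicts no direction or size. The 10.2 cm case needs no effect in one level and, from a baseline of about 5.1/0.15 = 34 cm, a gain of 30% in the other; the cited jump study reported 11.2%. Short of that, the loss is about 1 to 3 points. The protocol never says that 6.5 cm is a within-level SD, the 10 + 10 split is assumed, and the figures describe one unadjusted contrast instead of the full three-condition ANOVA.

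A reader might infer that the main test has the wrong type I error in general. The documents do not support that. The rate falls below 5% only if the levels respond in exactly offsetting directions, which no section suggests, and the omission does not push it above 5%.

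**Conclusion.** The point holds as a matter of efficiency. Leaving level out of the main ANOVA lets any level difference in the tDCS effect inflate the error of the active-versus-sham test. For a single part A contrast, under the assumptions listed, the cost relative to a model with level is about 0.5 points of power at a 2.55 cm level difference, 2.6 points at 5.1 cm and 12.6 points if one level does not respond at all. The 5.1 cm case takes power just below the 90% target. If 6.5 cm already includes level differences there is no shortfall against the plan, and the level term would be a gain.

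It would be wrong to read this as bias, as excess false positives or as an invalid test; none of these follows. For part B only the mechanism carries over.

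**What to change.** In Data management and statistical analyses, add athletic level (two levels in part A, three in part B) as a between-subject factor with its interactions with condition and moment. State that the condition x moment contrast is averaged over levels with equal weights and tested against the within-level error. Keep the by-level estimates descriptive, as now planned.

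The cost is one sentence and, for each contrast, one error degree of freedom in part A and two in part B. In part A that is about 0.2 points of power if the levels do not differ. Level is already recorded for everyone because allocation uses it, so no new data or participants are needed.

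It would also help to state the number per level and whether 6.5 cm is meant as a within-level or a total SD.

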## Methods/design

### Study setting and overview

This research will be carried out through a collaboration between the Psychiatric Department of the University Hospital of Besançon and the scientists from the Faculty of Sports of the University of Besançon (C3S Laboratory). All experiments will take place on the EPSI research platform (Entraînement Performance Santé Innovation, Besançon, France). This protocol will be divided into two parts to explore the effects of tDCS by type of exercise:
Part A, which assesses the effects on explosive performance (jumps)Part B, which assesses the effects on endurance performance (cycling time trial)

Fifty subjects (20 in part A, 30 in part B) will be recruited from the university or from federated organisations of sports. For part A, athletes practicing parkour, an activity that consists of jumping obstacles in various environments, have been chosen since they usually present a very explosive neuromuscular profile [24]. For part B, amateur and professional cyclists will be recruited. After information about the study, written informed consent will be obtained.

In part A, subjects will be divided into two groups (amateur vs high-level practice) and receive three sessions of tDCS (active over the left dlPFC vs active over the right M1 vs sham over the left dlPFC). The session order will be randomised (Fig. 1).

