With those stimulation parameters, stimulations at maximal H-reflex and M-waves will also be superimposed to maximal voluntary contractions (MVC), H_SUP_ and M_SUP_, respectively. It can be noticed that M_SUP_ is followed by a V-wave, which is used as an index of the supra-spinal descending neural drive [28]. To perform MVCs and record plantar flexor force, the ankle will be firmly strapped to a pedal equipped with a constraint gauge (PCE Instruments, France). Participants will be asked to focus on plantar flexion, avoiding any other unnecessary movement. The recording of one antagonist (TA) and one knee extensor (VL) will allow us to minimise the contribution of other muscle groups to the developed force. Participants will be asked to perform four MVCs of 4 s (two for H_SUP_ and two for M_SUP_), during which stimulations will be manually triggered during the force plateau. MVCs will separated by a minimum of a 1-minute rest.

The mechanical signals will be digitised online (sampling frequency 2 kHz) and simultaneously recorded with electromyography of the targeted muscles. Signals will be stored for analysis in Labchart software (LabChart 8, ADInstruments, Sydney, Australia).

Peak-to-peak amplitudes of electromyographic responses at rest (H_50_, H_MAX_, M_MAX_) and during MVC (H_SUP_, M_SUP_, V) will be measured for quantitative analysis. It can be noticed that maximal H-reflex, reflecting spinal excitability, is generally associated with a small M- wave (MatH at rest and MatHsup during MVC), which will also be measured. For each muscle, all responses will be normalised to maximal M-wave evoked in the same condition. Thus, H_50_/M_MAX_, H_MAX_/M_MAX_, M_atH_/M_MAX_, H_SUP_/M_SUP_, M_atHsup_/M_SUP_, and V/M_SUP_ will be considered as dependent variables.

In part A, each variable of the neuromuscular assessment will be performed before and after each tDCS session. In part B, it will be performed before and after the first sequence of tDCS, then at day 12 and day 30 for each sequence of the crossover.

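### Single-step Bonferroni is valid, but Holm's step-down procedure holds the same familywise error and never rejects less; the gain runs from nothing to about 12 points of power for two contrasts, depending on which effects are real

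*Protocol article*

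**What the plan says.** Under Data management and statistical analyses, the protocol article plans two-way repeated-measures ANOVAs (condition by moment) and adds that "Bonferroni corrections will be employed to correct for type I errors due to multiple testing". The significance level is 0.05, and 95% intervals are promised for means and proportions.

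Part A gives each jumper "three sessions of tDCS (active over the left dlPFC vs active over the right M1 vs sham over the left dlPFC"), so more than one contrast is possible. The Background section names a single main comparison: "The main objective is to compare the effects of tDCS applied over the left dlPFC with sham tDCS". The Neuromuscular assessment section lists six normalised evoked-potential ratios that "will be considered as dependent variables".

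The Sample size section rests on one paired difference at the full 5% level: "Considering a significance level of 5%, a power of 90%, and a standard deviation for paired differences of 6.5". The expected effect is given as "We expect a 15% improvement in our study corresponding to a difference of 5.1 cm", with "No difference is expected in the sham tDCS group".

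**The concern.** Bonferroni compares each of m p-values with 0.05/m. Holm compares the smallest with 0.05/m, the next with 0.05/(m − 1), and so on, stopping at the first failure. Both control the familywise error at 5% whatever the dependence between tests. Every Bonferroni rejection is also a Holm rejection, and the reverse need not hold. The article therefore names a method that has a replacement with the same error guarantee and power at least as high, whichever tests form the family.

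With only 20 jumpers, power is scarce. The cost of Bonferroni is a real second effect that misses 0.025 but would have passed 0.05 once the first had been established.

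**Working it through.** **Inputs from the article (Sample size section):** n = 20, effect 5.1 cm after active stimulation, 0 after sham, SD of a pre-post difference 6.5 cm, 5% level, 90% power.

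**Reproducing the stated sample size.** For a two-sided paired t test, the noncentrality is 5.1 / (6.5/√20) = 3.51. Power is 91.4% at n = 20 and 89.8% at n = 19, so the stated 20 reproduces for one test at an unadjusted 5%.

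**Assumptions that the article does not supply.**
- The family is two contrasts: each active site versus sham, on pre-post changes.
- Motor cortex stimulation also gains 5.1 cm. The alternative case is no gain.
- Changes in different sessions correlate r. The contrast SD is then 6.5 × √(2(1 − r)): 9.19 cm at r = 0, 7.96 cm at r = 0.25 and 6.5 cm at r = 0.5. The two contrasts share sham and so correlate 0.5.

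**Decision rules for two tests.** Bonferroni rejects contrast 1 if p1 ≤ 0.025. Holm rejects it if p1 ≤ 0.025, or if p1 ≤ 0.05 and p2 ≤ 0.025. The per-contrast gain is therefore P(0.025 < p1 ≤ 0.05 and p2 ≤ 0.025). By symmetry, the gain for rejecting both is twice that. The event of rejecting at least one is identical under the two rules.

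**Simulation** (200,000 trials per scenario, n = 20, both contrasts truly 5.1 cm; gains taken before rounding):

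| r | Contrast SD | Per contrast, Bonferroni → Holm | Both, Bonferroni → Holm | At least one |
|---|---|---|---|---|
| 0 | 9.19 | 53% → 59% (+6.1) | 36% → 48% (+12.2) | 70%, no change |
| 0.25 | 7.96 | 67% → 73% (+6.2) | 51% → 64% (+12.4) | 82%, no change |
| 0.5 | 6.5 | 85% → 90% (+4.6) | 75% → 85% (+9.2) | about 94%, no change |

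The gain for both is twice the per-contrast gain in each row, as it should be.

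**Only one site works.** At SD 9.19, power for that contrast goes from 53.0% to 53.2%. At SD 6.5 it goes from 84.9% to 85.1%. The gain is about 0.2 points in each case.

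**Error rate.** With one true null, familywise error was 2.5% for Bonferroni and 3.9% to 4.5% for Holm. With both nulls true it was about 4.7% for each. No simulated trial had a Bonferroni rejection that Holm missed.

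**Other families.** If all three pairwise contrasts are tested and two differences are real, the gain is 3.3 to 3.5 points per real contrast and 6.6 to 6.9 for both. With three separate tests, each truly 5.1 cm with SD 6.5 and correlations of 0.8 down to 0, it is 6.1 to 9.3 per test and 14.0 to 23.9 for all three. With one real effect among three it is again 0.1 to 0.2.

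**What Holm leaves untouched.** The first rejection still faces 0.05/m. With SD 6.5 and n = 20, that step has 84.9% power for two tests (23 subjects needed for 90%) and 80.1% for three (25 needed).

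**The case against.** The strongest reply is that nothing here is wrong. Bonferroni delivers the error control it is meant to deliver, no other statement in the article contradicts it, and the trial calls itself exploratory. The main objective is one contrast, and in a family of one the two methods are the same. Part B compares only active with sham, so it too has one condition contrast. All of this stands, and it is why the point is an efficiency improvement and not a defect.

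A reader might infer that the plan's own inputs show a loss of 6 to 12 points that could be recovered at no cost. The documents do not support that. The family, the motor cortex effect and the active-minus-sham SD are all assumed. The lower figure is power per contrast and the upper is power for both, so the range mixes two quantities. Both presume that the two sites work equally well, which favours Holm.

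A reader might also extend the argument to the six evoked-potential ratios. The ANOVA sentence names only endurance and explosive performance, and the article gives no effect sizes or correlations for the ratios, so no gain for them can be drawn from it.

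Finally, Bonferroni has simple matching simultaneous confidence intervals and Holm does not. This is a real if small cost. The article promises only ordinary 95% intervals, so nothing it states would be lost.

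**Conclusion.** The point holds as a cheap improvement. Whatever the family, Holm is never less powerful than the stated method at the same familywise error.

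Its size depends on how many effects are real. For two contrasts against sham, both truly 5.1 cm with n = 20, the gain is about 5 to 6 points per contrast and about 9 to 12 for establishing both, across change-score correlations of 0.5 to 0. If only one site works it is about 0.2 points. It is zero for establishing at least one effect and zero in a family of one, so it does little for the left dlPFC comparison unless that contrast is tested alongside others that are also real. The mathematical ordering of the two methods is certain; the size of the gain rests on the assumptions listed.

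**What to change.** Replace the Bonferroni sentence, before unblinding, with: *Within each family of tests, p-values will be adjusted by the Holm step-down procedure at a familywise level of 5%.*

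The cost is one sentence and one software option, plus the loss of simple matching simultaneous intervals. Recruitment, data and the overall error level do not change. The sentence needs the families to be named wherever the full plan sets them out, as the Bonferroni sentence already does. The change should not be presented as a remedy for the unadjusted 5% level in the sample size, which is a separate matter.
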